### Addressing Aim 1: Target trial emulation

#### Target trial design

A hypothetical target trial will be emulated in which young men and women taking valproate would be randomised to either continue valproate, switch to lamotrigine or levetiracetam, or discontinue valproate [21]. The following mortality and morbidity outcomes would be assessed over the subsequent five years:

Deaths (all-cause/epilepsy-related);ED/hospital admissions (all-cause/epilepsy-related);Seizures (symptom codes);Falls;Injuries;Burns;Aspiration pneumonia;Manic/bipolar episodes;New-onset depression;Self-harm/suicide;A composite morbidity index incorporating seizures, injuries, admissions, depression.

Intention-to-treat (ITT) and per-protocol effects would be assessed between groups [21]. Analysis would take a time-to-first-event approach (Cox-proportional hazards model) for deaths, new-onset depression and composite morbidity. A recurrent events approach (e.g., Prentice-Williams-Peterson Total Time Model) would be taken for the remaining outcomes.

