#### Target trial emulation using observational data from TriNetX and CPRD

*Eligibility criteria*. Anonymised, person-level, electronic health data will be extracted from TriNetX and CPRD, linked across primary care, ED, inpatients, outpatients, and mortality subsets. The study period will be from 01/01/2014 to 01/01/2024. Included will be men and women aged 16–54 years. The study will take an open cohort design with patients entering the cohort when the following criteria are met:

Either: ≥1 epilepsy disease or symptom code recorded during the study period and two separate valproate prescription instances over the preceding 12 months before at least one of the epilepsy disease or symptom codes;

Or: ≥1 epilepsy disease or symptom code recorded any time before the study period with at least two separate valproate prescription instances over 12 months during the study period.

TriNetX and CPRD use ICD-10-CM and SNOMED codes, respectively. The coding strategy combining disease and symptom codes with valproate, as used our published study successfully [20], was shown to accurately identify epilepsy cases in our prior work [28,29].

Treatment arms:

Withdrawn valproate and commenced lamotrigineWithdrawn valproate and commenced levetiracetamWithdrawn valproate and no new ASM commencedContinues valproate

*Treatment assignment*. Baseline (time 0) will be defined as when valproate dose reduction commences (treatment arms 1–3) or prescription of valproate at a matched time (arm 4). Eligible individuals are assigned at baseline to the treatment strategy that their data are consistent with [21]. To emulate randomisation, adjustment is made for baseline confounders using Robins’ generalised methods (g-methods, e.g., inverse probability weighting) [21], considering age, sex, ethnicity, deprivation, type of epilepsy (using G40 codes), baseline seizure frequency (symptom codes recorded over preceding 12 months), alcohol excess, developmental delay, Cambridge Multimorbidity Score, length of valproate treatment, valproate dose, and ASMs used other than valproate. The final set of covariates required to adjust for confounding will be chosen using a causal directed acyclic graph [21].

*Outcomes*. These are listed in the target trial design section and derived from our prior work [1,20,30,31], and public consultation. All coded events will be recorded for flexible categorical or continuous analyses, as needed.

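### Seizures are counted by symptom codes alone, both as an outcome and as the baseline severity adjuster, so an acute seizure coded only as epilepsy is missed in both

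*Protocol article*

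**What the plan says.** The outcome list in the protocol article (Methods, Target trial design) gives "Seizures (symptom codes"). The covariates for emulating randomisation (Target trial emulation using observational data, Treatment assignment) include "baseline seizure frequency (symptom codes recorded over preceding 12 months").

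Disease codes are treated as a separate family and used for other purposes:

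- Cohort entry needs "≥1 epilepsy disease or symptom code recorded during the study period", or such a code before the study period, together with valproate prescriptions.
- The epilepsy-type covariate is "type of epilepsy (using G40 codes").
- The validation claim concerns diagnosis: "The coding strategy combining disease and symptom codes with valproate" "was shown to accurately identify epilepsy cases in our prior work".

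Two other outcomes touch the same events: "ED/hospital admissions (all-cause/epilepsy-related") and "A composite morbidity index incorporating seizures, injuries, admissions, depression". The composite in the prediction-model section also contains seizures and admissions.

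**The concern.** Everyone in the cohort has epilepsy, so the reason for an acute attendance can be recorded as the disease instead of as a seizure. Under the stated rule, a breakthrough seizure in ED coded only as epilepsy gives one epilepsy-related attendance and no seizure. The same attendance coded as a seizure gives one seizure. The event is also lost from the 12-month baseline count if it falls before time 0.

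Two uses of the data are exposed:

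- **Absolute risks.** The Pathways to impact section intends the Aim 1 figures for the part of the NHS England decision tool that tells patients their own risks from a medication change. Figures of that kind depend on how completely seizures are captured.
- **Confounding control.** Baseline seizure frequency is one of the listed confounders and the only one that directly measures recent seizure activity. If it is under-measured, weighting on it balances the arms only in part.

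**Working it through.** **1. The plan's own figure.** Table 1 uses ED attendance: p1 = 2977/8021 = 0.3712 (withdrawn) and p2 = 2471/8021 = 0.3081 (remaining), two-sided alpha 0.05, power 0.80.

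n = 7.849 × (0.2334 + 0.2132) / 0.0631² = 880.7, rounded up to 881. This matches the stated 881. The calculation does not use seizures, so it is unaffected by this point.

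**2. What the rule counts.** Setting the passages side by side:

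| Acute contact coded as | Seizure outcome | Baseline seizure count | Epilepsy-related ED/admission |
|---|---|---|---|
| Seizure symptom code | counted | counted | depends on its definition |
| Epilepsy disease code only | not counted | not counted | counted |

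The document gives no symptom-code list, no share of seizures recorded only as disease, and no sensitivity for the seizure outcome. Everything below is therefore illustrative.

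**3. Outcome capture.** Assumption: 0.371 and 0.308, which are ED proportions, stand in for true seizure risks. A fraction s of events is captured, so observed risk = s × true risk.

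| Capture, withdrawn / continuing | Observed risks | Difference | Ratio |
|---|---|---|---|
| 100% / 100% | 0.371 / 0.308 | 0.063 | 1.20 |
| 80% / 80% | 0.297 / 0.246 | 0.050 | 1.20 |
| 50% / 50% | 0.186 / 0.154 | 0.032 | 1.20 |
| 70% / 50% | 0.260 / 0.154 | 0.106 | 1.69 |
| 50% / 70% | 0.186 / 0.216 | −0.030 | 0.86 |

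Equal under-capture scales risks and differences by s and cancels from the ratio. Unequal capture moves the ratio in either direction.

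**4. Baseline capture, equal in both arms.** Let π be the true proportion of an arm with a recent seizure before time 0. Among those with no recorded seizure, the proportion who truly had one is

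h = π(1 − s) / (1 − πs).

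Adjustment treats this group as alike. Using 0.371 and 0.308 again as stand-ins for π (which arm is higher is arbitrary):

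| s | h, first arm | h, second arm | Difference |
|---|---|---|---|
| 1.0 | 0 | 0 | 0 |
| 0.7 | 0.111/0.740 = 0.150 | 0.092/0.784 = 0.118 | 0.033 |
| 0.5 | 0.186/0.814 = 0.228 | 0.154/0.846 = 0.182 | 0.046 |
| 0.3 | 0.260/0.889 = 0.292 | 0.216/0.908 = 0.238 | 0.055 |

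Imbalance in hidden seizures therefore remains after adjustment, although coding is identical in both arms, and it grows as capture falls. If people with a hidden seizure have R times the later risk of the others, the spurious ratio in this group is (1 + h1(R − 1)) / (1 + h2(R − 1)). The document does not give R. At s = 0.5 the ratio runs from 1.00 (R = 1) towards a ceiling of 0.228/0.182 = 1.25, or the reciprocal if the other arm has more baseline seizures.

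**5. Composites.** Both composites contain admissions, and both are analysed as time to first event. A disease-coded seizure that counts as an admission already ends follow-up on its own date, so also labelling it a seizure changes nothing. Only contacts that do not count as admissions are at risk of being lost.

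**The case against.** The strongest reply is that symptom codes are a deliberate choice for specificity. In an all-epilepsy cohort a disease code may repeat the standing diagnosis at a routine contact, and counting every such code would inflate seizures. Identifying a diagnosis and dating an event are different tasks, so different code sets are not a contradiction. The epilepsy-related ED/admission outcome already picks up the disease-coded acute events. The article says that all coded events will be recorded and that outcome coding algorithms will be published, so a wider definition remains possible. False-positive symptom codes could also offset some of the loss.

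Much of this stands. It rules out adding disease codes without restriction, and it means the size of the loss is unknown. It does not help the stand-alone seizure outcome or the baseline count, because the text fixes both to symptom codes and the listed covariates include no prior epilepsy-related attendance or admission. The cited validation covers identifying epilepsy cases. None is cited for symptom codes as a count of seizures.

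Three stronger readings are tempting and are not supported:

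- **Seizure risk after withdrawal specifically is understated, or the contrast is biased in a known direction.** One code rule applies to all arms. Any loss lowers risk in continuers too, and nothing in the document shows that coding differs by arm.
- **The plan requires both code families at entry and then drops one for the outcome.** Eligibility accepts either.
- **The composites are seriously damaged.** They include admissions, as step 5 of the working shows.

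**Conclusion.** The point holds in a limited form. As written, an acute seizure contact coded only as epilepsy is absent from both the seizure outcome and the baseline seizure frequency. If the captured share is s in all arms, absolute seizure risks and risk differences are s times their true values, so 50% capture halves them. The outcome ratio is unchanged by this alone. Under-measurement of the baseline count can leave residual confounding even when capture is equal. That requires true baseline seizure activity to differ between arms and to predict later seizures, which is the plan's own reason for adjusting for it. The sign depends on which arm has more baseline seizures.

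All sizes here rest on assumed capture shares and on ED proportions used as stand-ins; the document supplies neither seizure rates nor coding sensitivity. This is a worthwhile and inexpensive improvement, not a demonstrated bias in the main comparison.

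**What to change.** Before data extraction, define a second seizure measure: any seizure symptom code, or an ED attendance or unplanned admission that the plan's existing outcome definition classes as epilepsy-related.

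- Use this measure for the 12-month baseline severity adjustment. Alternatively, keep the symptom-code count and add prior epilepsy-related ED attendances and admissions as a covariate.
- Report the seizure outcome under both definitions and pre-specify which is main.
- The composites need no change on this account.

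The cost is a wider code list, built largely from codes already needed for the epilepsy-related ED/admission outcome. The article says that data access is still being sought, so this can be settled in time. The drawbacks are overlap between the wider seizure measure and the epilepsy-related ED/admission outcome, and some epilepsy contacts without a seizure being counted. Reporting both definitions shows how much either matters.

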*Causal estimand*: Assesses impact of treatment arms 1–3 vs. 4 on outcome (per-protocol assumption as observational data limits ITT assessment) [21].

*Start and end of follow-up*. The start of follow-up (Time 0 or index date) will be defined as when valproate treatment discontinued (treatment arms 1–3) or prescription of valproate at a matched time (arm 4). For time-to-first-event analyses, the end of follow-up will be defined as when the outcome occurs, censoring (including deviation from assigned treatment or leaving the study catchment area), or 10 years. For recurrent events analyses, alongside censoring as above, the end of follow-up will be 10 years, allowing for all events to be assessed throughout follow-up.

*Statistical analysis*: mirrors target trial section.

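### Self-harm and suicide are listed as one outcome and sent to the recurrent-events analysis, so no stated analysis shows suicide on its own

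*Protocol article*

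**What the plan says.** The outcome list in the protocol article (Methods, Target trial design) includes "Manic/bipolar episodes;New-onset depression;Self-harm/suicide". Self-harm and suicide share one entry.

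The same section divides the outcomes between two analyses. The time-to-first-event analysis is given as "Cox-proportional hazards model) for deaths, new-onset depression and composite morbidity". For everything else, "A recurrent events approach (e.g., Prentice-Williams-Peterson Total Time Model) would be taken for the remaining outcomes". Self-harm/suicide is not among the three outcomes named for first-event analysis, so it falls in the recurrent group.

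The emulation section keeps this split: its statistical analysis "mirrors target trial section". On follow-up it states: "For recurrent events analyses, alongside censoring as above, the end of follow-up will be 10 years, allowing for all events to be assessed throughout follow-up". The reasons for ending follow-up early are given as "censoring (including deviation from assigned treatment or leaving the study catchment area"), and death is not mentioned as a terminal or competing event. Mortality is listed as "Deaths (all-cause/epilepsy-related"), without a suicide-specific category.

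**The concern.** A completed suicide is a death. It happens once and removes the person from all later risk. The protocol follows that logic for deaths, which get a first-event analysis, but places the same event in the recurrent class when it is labelled suicide.

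Two consequences follow if self-harm and suicide are counted together. One suicide then carries the weight of one self-harm code, so a difference in suicide is hard to see. Suicide also selectively removes people prone to repeat self-harm, so it is an informative end to the recurrent process.

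The Introduction and Pathways to impact sections say that the study should fill the part of a national decision tool that covers personal risks of changing medication. A pooled ratio near 1 could be read there as showing no suicide signal, when the analysis had little capacity to show one.

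**Working it through.** The protocol gives no rate, effect size or sample size for self-harm or suicide, so there is no figure of its own to reproduce on this point. Its sample size rests on emergency department attendance and is not involved. All rates below are assumptions, shown over a range.

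**1. Allocation.** Named for first-event analysis: deaths, new-onset depression, composite morbidity. Self-harm/suicide is not named, so it is recurrent. The named model is only an example, but the recurrent class is fixed.

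**2. Dilution in a pooled count.** Let there be k self-harm events per suicide in the comparison arm. Assume no effect on self-harm and a doubling of suicide in the other arm. The pooled ratio is (k + 2)/(k + 1).

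| k (assumed) | Calculation | Pooled ratio |
|---|---|---|
| 10 | 12/11 | 1.09 |
| 25 | 27/26 | 1.04 |
| 50 | 52/51 | 1.02 |

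A wider grid takes self-harm at s = 0.005 to 0.05 and suicide at f = 0.0002 to 0.002 per person-year. The ratio (s + 2f)/(s + f) then runs from 0.0504/0.0502 = 1.004 to 0.009/0.007 = 1.29. Suicide analysed separately would show a ratio of about 2.

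**3. Would a combined first-event endpoint help?** With constant hazards s and f, the hazard of the first of either event is s + f in one arm and s + 2f in the other. The hazard ratio is again (s + 2f)/(s + f), which equals (k + 2)/(k + 1) with k = s/f. At k = 25 it is still 1.04. The dilution therefore comes from pooling, not from the recurrent model.

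**4. Lost person-time.** Mean follow-up over T = 10 years is (1 − exp(−fT))/f.
- f = 0.002: 9.901 years. Doubled to 0.004: 9.803 years. Loss: 1 − 9.803/9.901 = 1.0%.
- f = 0.0002: the same calculation gives a loss of 0.1%.

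This is negligible.

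**5. Informative removal.** A simulation used a gamma frailty shared by self-harm and suicide (variance 4 or 10), s = 0.02, f = 0.0005 to 0.002, 10 years, suicide hazard doubled and no true effect on self-harm. The self-harm rate ratio fell to between 0.93 and 0.99, and the combined ratio was 1.00 to 1.05. These are crude rates per person-year, not estimates from the named model, and they depend on the assumed frailty variance. They show the direction, and that the effect can cancel some or all of the small pooled signal.

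**The case against.** The strongest objections are these.

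- **The slash may not mean pooling.** The deaths entry also uses a slash, for two versions of an outcome. If self-harm and suicide are two outcomes, nothing is diluted; with at most one event per person, the Prentice-Williams-Peterson model reduces to an ordinary Cox model. If suicide means attempt codes, recurrence is sensible. This stands as an ambiguity, and the dilution figures are therefore conditional on pooling. The text settles neither reading, so clarification is needed either way.
- **Suicides are not lost.** They enter all-cause death, which has a first-event analysis, and the emulation section adds: "All coded events will be recorded for flexible categorical or continuous analyses, as needed". This is true, but all-cause death mixes suicide with every other cause, and the clause keeps the data without stating a suicide analysis.
- **Detail may sit in an unseen analysis plan.** Component reporting and terminal-event handling often do, so their absence alone is not the point. The allocation of this outcome to the recurrent class is stated in the article.

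A reader might also infer stronger claims that the documents do not support. One is that the recurrent model itself causes the dilution, so that moving the combined outcome to the first-event list would repair it; step 3 shows otherwise. Such a move would also discard any suicide preceded by a self-harm code after baseline. A second is that lost person-time hides the difference; it is about 1% or less, and a hazard model already removes the dead from the risk set. A third is that every recurrent-events model fails here. Models with a terminal event exist, and the article's wording leaves them open.

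**Conclusion.** The point holds in a limited form. As written, an outcome that includes completed suicide is assigned to the recurrent-events class, and no stated analysis shows suicide on its own. If the two are pooled, a doubling of suicide appears as about 1.09 to 1.02 for 10 to 50 self-harm events per suicide, or 1.29 to 1.004 over the wider grid. These sizes rest on assumed rates and on no effect of withdrawal on self-harm. They are crude rate ratios rather than Prentice-Williams-Peterson estimates. Informative removal by suicide is a secondary concern whose size is uncertain.

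Severity is low to moderate. This is one of many outcomes; it is not a named component of the composite morbidity index and does not drive the sample size.

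**What to change.** Split the entry in the outcome list and amend the analysis paragraph.

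- **Suicide:** analyse as a cause-specific death by time to event, beside all-cause and epilepsy-related death, with other deaths as competing events.
- **Non-fatal self-harm:** keep in the recurrent-events analysis, with death handled as a terminal event.
- **Definition:** state whether the suicide codes cover completed suicide only, or attempts as well; attempts belong with non-fatal self-harm.

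The cost is a few lines of wording. The eligibility paragraph already plans linked mortality data, and the epilepsy-related death outcome already requires a cause of death. If suicide cannot be identified as a cause in one of the databases, the report should say so. The main downside is that suicide alone will have wide intervals, so it should be presented as imprecise and not as evidence of no difference.

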### Sample size calculation

See Table 1.

**Table 1 pone.0306226.t001:** Sample size calculation.

Outcome: Emergency department attendance (a global measure of morbidity and a good predictor of mortality) Data source: Mbizvo *et al*. [20]			
**Target trial emulation phase**		**Prediction model phase**	
**Method**	# Proportions from the pilot study p1 <- 2977 / 8021 # valproate withdrawn group p2 <- 2471 / 8021 # group remaining on valproate # Set significance level and power alpha <- 0.05 power <- 0.80 # Z-values for two-tailed test z_alpha <- qnorm(1—alpha / 2) z_power <- qnorm(power) # Calculate sample size n <- ceiling((z_alpha + z_power)^2 * ((p1 * (1—p1)) + (p2 * (1—p2))) / (p1—p2)^2) # Display the result cat("Sample size needed for the target trial emulation study:", n, "\n")	**Method**	Sample size criteria from our previous work for developing a time-to-event prediction model to estimate the minimum required sample size for our model development are used [33].
**Result**	The minimum sample size in the target trial emulation study is 881.	**Assumptions**	
		**(i)**	We target an overall shrinkage factor of 0.9.
		**(ii)**	We assume the outcome rate to be 0.068, calculated using the 5,448 events that occurred out of 16,042 patients within the pilot study, with a median survival time of 5 years.
		**(iii)**	The performance of the model would achieve 15% of the maximum possible cox-snell R-squared for the given outcome rate.
		**(iv)**	We would consider 20 candidate predictor parameters within the model development process.

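### The only recurrent-event model named, Prentice-Williams-Peterson total time, conditions on post-baseline event counts, so it does not target the total effect of withdrawal and typically understates a real one when patients differ in event risk

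*Protocol article*

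**What the plan says.** The section Target trial design lists eleven outcomes. Deaths, new-onset depression and composite morbidity are analysed by time to first event. For the other eight (ED/hospital admissions, seizures, falls, injuries, burns, aspiration pneumonia, manic/bipolar episodes, self-harm/suicide), "A recurrent events approach (e.g., Prentice-Williams-Peterson Total Time Model) would be taken for the remaining outcomes". No other recurrent-event model is named.

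In the emulation section, the statistical analysis "mirrors target trial section". The causal estimand there "Assesses impact of treatment arms 1–3 vs. 4 on outcome", on a per-protocol basis. To emulate randomisation, "adjustment is made for baseline confounders using Robins’ generalised methods (g-methods, e.g., inverse probability weighting". The covariates include "baseline seizure frequency (symptom codes recorded over preceding 12 months", epilepsy type and a multimorbidity score.

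The article uses two horizons. Target-trial outcomes "would be assessed over the subsequent five years", whereas in the emulation "For recurrent events analyses, alongside censoring as above, the end of follow-up will be 10 years", with censoring at deviation from assigned treatment.

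**The concern.** In the total-time model a patient enters the risk set for event k only after event k−1. Membership of every stratum after the first is thus decided after time 0, by something treatment may change. If withdrawal raises the event rate, lower-risk patients reach stratum k more readily in the withdrawn arms than in the continuing arm. The withdrawn patients in that stratum are then, on average, at lower underlying risk. Baseline weighting balances the arms at time 0, not within strata formed later, and a perfectly randomised trial would lose comparability in the same way. The model also removes any harm that runs through earlier events, for instance where one seizure makes the next more likely.

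Aim 1 asks whether outcomes differ between staying on valproate and withdrawing, which is a question about the total effect. The Pathways to impact section intends the Aim 1 figures for the personal-risk section of a national decision tool, so understating harm from withdrawal would matter there.

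**Working it through.** **The plan's own figure.** Table 1 gives p1 = 2977/8021 = 0.3712 (withdrawn) and p2 = 2471/8021 = 0.3081 (continuing), alpha 0.05 ("Z-values for two-tailed test") and power 0.80. The printed formula gives (1.960 + 0.842)² × (0.2334 + 0.2132) / 0.0631² ≈ 880.7, so 881. This reproduces. It compares proportions and does not depend on the recurrent-event model.

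**Calibration to Table 1.** Assume each patient has Poisson events with a constant rate multiplied by a gamma frailty of mean 1 and variance v. Then the chance of at least one event in 5 years is 1 − (1 + vΛ)^(−1/v), where Λ is the mean 5-year count. Hence Λ = [(1 − p)^(−v) − 1]/v, or −ln(1 − p) when v = 0. With 1 − p2 = 0.6919 and 1 − p1 = 0.6288:

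| v | Λ continuing | Λ withdrawn | True rate ratio |
|---|---|---|---|
| 0 | 0.368 | 0.464 | 1.26 |
| 0.5 | 0.404 | 0.522 | 1.29 |
| 1 | 0.445 | 0.590 | 1.33 |
| 2 | 0.544 | 0.764 | 1.40 |

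The article gives no dispersion and no recurrent-event rates. The values of v, the Poisson form and constant rates to 10 years are assumptions.

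**Simulated randomised comparison at those rates.** Excess lost = (true − estimate)/(true − 1).

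| v | True | Named model, 5 y | Lost | Named model, 10 y | Lost |
|---|---|---|---|---|---|
| 0.5 | 1.29 | 1.24 | 0.05/0.29 = 17% | 1.24 | 0.05/0.29 = 17% |
| 1 | 1.33 | 1.25 | 0.08/0.33 = 24% | 1.21 | 0.12/0.33 = 36% |
| 2 | 1.40 | 1.24 | 0.16/0.40 = 40% | 1.19 | 0.21/0.40 = 53% |

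At v = 0 there is no loss. A separate set of runs gave losses of 14%, 20% and 42% at 5 years and 22%, 34% and 53% at 10 years, so the figures are good to a few percentage points. In that set the unstratified (Andersen-Gill) model gave 1.28, 1.32–1.33 and 1.38–1.41 for v = 0.5, 1 and 2, close to the true values.

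**Direction in other settings.**
- True ratio 1.00: the named model stays at 1.00.
- No frailty, each of the first three events multiplying later risk by 1.5: 1.30 against a total effect of 1.43.
- No frailty, events lowering later risk (factor 0.7): 1.27 against 1.23, so further from the null.

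**Does the alternative survive the censoring rule?** Assume 0.3 events per person-year, v = 1, and deviation from assigned treatment after each event in 20% (continuing) or 50% (withdrawn).

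| True ratio | Named model | Unstratified, unweighted | Unstratified, event-history censoring weights |
|---|---|---|---|
| 1.00 | 1.00 | 0.86 | 0.98 |
| 1.30 | 1.19 | 1.06 | 1.28 |

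**The case against.** The strongest objection is that the article fixes only a recurrent-events approach. The model is an example in a condensed article, and the final choice may lie in a fuller plan. That stands as to status: nothing is locked. It does not remove the point, because this is the one model named, the emulation adopts it, and it does not match the estimand the article states.

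A reader might infer that the model always biases towards no difference. The runs above do not support that. The direction depends on heterogeneity or on how events affect later risk, and under a true null the model showed no distortion, so Hypothesis 1 stays testable, with less sensitivity.

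A reader might also expect a larger loss. At an assumed 0.3 events per year and a true ratio of 1.30, the model gives 1.20, 1.17 and 1.13 for v = 0.5, 1 and 2, a loss of 33–57%. That rate implies 50–67% of continuing patients with an event in 5 years (for v = 1, 1 − 1/2.5 = 60%), against 31% in Table 1. For ED attendance the figure is therefore not supported. Outcomes rarer than ED attendance would lose less, and commoner ones more.

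Seizures, injuries and admissions also enter the composite and the Aim 2 model, both analysed by time to first event without event-order strata, so the problem does not reach every result. First-event hazard ratios are not immune to heterogeneity, however. In a run with true ratio 1.30, 0.1 events per year, 10 years and v = 1, the first-event estimate was 1.21 and the named model 1.19. Much of the gap there is thus already present in the first stratum.

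Finally, simply swapping models can make matters worse. If events prompt treatment changes, the unweighted marginal model can show withdrawal as protective when it has no effect (0.86). This objection stands in full and shapes the fix.

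**Conclusion.** The mismatch between model and estimand holds whatever the direction of the distortion: the named model conditions on a post-baseline consequence of treatment, while the article seeks the effect of arms 1–3 versus 4 on outcome. Attenuation is the likely practical result, because the article's own confounder list (seizure frequency, epilepsy type, multimorbidity) implies that patients differ in underlying event risk. At Table 1's event level, roughly 15–40% of the excess rate would be lost at 5 years and 20–55% at 10 years. This rests on assumed gamma frailty variances of 0.5 to 2, Poisson events, constant rates and full follow-up. The documents establish no single value.

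A reader might also infer that the sample size is undermined, or that false positive findings would follow. Neither is supported: 881 does not use this model, and a true null is preserved in these runs. The plan should be changed, but it is not invalid as it stands, since the model is offered only as an example.

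**What to change.** Name a marginal rate model as the main recurrent-event analysis: Andersen-Gill form, not stratified by event number, with patient-clustered robust variance. Report the weighted mean cumulative number of events by arm at fixed times, treating death as a terminal event.

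Fit it with the baseline treatment weights plus time-varying censoring weights whose model includes event history. The second set is essential because follow-up is censored at deviation from assigned treatment and the article describes adjustment for baseline confounders only. Keep the Prentice-Williams-Peterson model as a supplementary analysis, described as the effect on the next event given the same event history.

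No new outcomes or data sources are needed. The cost is an additional censoring-weight model, with its own assumptions: the measured history must explain deviation adequately, and the weights must not be extreme. The main analysis would no longer describe order-specific effects, which the aims do not ask for.
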